## Methods

### Participants and Trial Design

Participants were drawn from a sample of undergraduate college students at a large public university who previously participated in a large, campus-wide cross-sectional survey in Spring 2023 and agreed to be contacted for future research. Participants who indicated past-month alcohol use or lifetime marijuana, hashish, or Δ-8-tetrahydrocannabinol (THC) use or some combination thereof were sent an email inviting them to participate in this study. Individuals interested in participating contacted the study team for more information or moved directly to the screener questionnaire using unique REDCap (Research Electronic Data Capture; Vanderbilt University) survey links provided in their emails.

Individuals were eligible to continue into the study if their responses to the screener questionnaire indicated that they were 18-25 years of age, used alcohol and cannabis in the past 30 days, and used an iPhone with an iOS version of 12 or more recent. The iPhone eligibility requirement was added to overcome technical challenges and additional confounding elements related to variations in how REDCap surveys and visual messages are displayed in iOS versus Android systems. Previous work by the study team has shown that students in the current institution are overwhelmingly iPhone users.

Eligible participants who consented to participate in this study were randomized into either the EMA group or the EMA+DD group and directed to the baseline survey. The randomization was performed automatically such that each participant had a 50% chance of being assigned to either of the 2 groups. The team planned to collect data from at least 40 individuals in each study condition. Study team members were able to see participants’ group assignment but had no contact with participants at any time to avoid introducing interview bias. After completing the baseline survey, participants were automatically enrolled in the 21-day portion of the study, with day 1 starting on the first Thursday after baseline completion. During the 21-day portion of the study, the participants received text-based prompts with a personalized REDCap link to a web survey.

Each prompt was sent at 4 equally spaced times per day (11 AM, 2 PM, 5 PM, and 8 PM) for 21 days, for a total of 84 prompts for each participant. Assessment timing was fixed to ensure data collection protocol as identical between both groups, to allow time in between assessments or avoid stacking of assessments, and to accommodate typical sleeping schedules and timing of substance use among our sample of college students who use substances*.* At each prompt, participants reported their substance use since the last prompt, psychosocial factors, and whether they were using their phone at the exact moment of receiving each prompt. Participants were instructed to complete each survey within 60 minutes of receiving the link, at which point the link would expire. At the conclusion of the 21-day portion of the study, participants completed an exit survey to provide feedback on their experiences in the study, including the acceptability and usefulness of a DD (for the EMA+DD group) or their openness to receiving a DD (for the EMA group).

### Real-Time Data Dashboard Intervention: an MRT Design

For individuals in the EMA+DD group, 1 of the 4 prompts on each day included a DD component plus a personalized message, whereas the other 3 prompts simply presented the standard text with a link to the survey. Within each day, the prompt at which the DD would be delivered was selected at random. Figure 1 depicts the data collection schedule and corresponding compliance, as experienced by 5 random participants in each condition.

**Figure 1 figure1:**
[figure not shown]
Data collection schedule and corresponding compliance data from 10 random study participants: 5 in the EMA+DD group (top panel) and 5 in the EMA group (bottom panel). Each row represents 1 participant, and each cell represents 1 day. Cell shading indicates EMA completion by the participant (blue=completed, gray=missing), and dots indicate display of the DD to the participant (black=DD without completion bonus progress ring, red=DD with completion bonus progress ring). DD: data dashboard; EMA: ecological momentary assessment.

Our DD included several features to convey a participant’s study compliance. The visual image for the DD was partly inspired by the progress charts or exercise rings commonly found on wearable smart devices and fitness trackers (eg, Apple Watch and Garmin devices). Multiple iterations of the DD were tested internally by the study team to confirm accuracy and ensure that the information was user-friendly. The DD comprised 2 separate rings in the form of concentric circles. The outer ring (blue) represented the number of surveys that have been completed; the inner ring (red) represented the number of days (out of 21) completed. The colored parts (nongray areas) of the ring provided a visual representation of study compliance to date and were labeled with a count of the prompts and days completed to that point. Once participants completed at least 50% of their daily surveys, a portion of the outer ring turned yellow. The yellow portion indicated the number of surveys remaining before the participant reached a high completion bonus; the number of remaining surveys also was shown in the yellow portion of the ring. Color-matched text below the visual image provided a key to interpret the rings, with blue text showing the number of surveys completed, red text showing the number of days left in the study, and yellow text showing the number of surveys left before achieving the bonus (only when the bonus event activated, as described above). The center of the rings represented a “bank,” displaying the total amount of incentive money the participant had earned to that point in the study. The participant’s name also was generated on each DD as a form of personalization (eg, “[Name’s] progress so far!”). Colors for the rings were selected from a color palate that is more distinguishable for individuals with colorblindness.

Figure 2 shows a hypothetical example of the real-time, personalized DD that accompanied 1 randomly selected prompt per day among individuals randomized to the EMA+DD group. This example shows data for a hypothetical individual on day 15 who had completed 42 prompts, conveying the participant’s progress in the study to date. Specifically, the DD shows the number of prompts completed so far, the number of days remaining in the study, the number of surveys remaining until they earn the high completion bonus, and the total amount of incentives earned to date.

**Figure 2 figure2:**
[figure not shown]
Example of a data dashboard that accompanied a text prompt to complete an ecological momentary assessment survey for a hypothetical participant who had completed 15 days of the study, provided data in response to 42 prompts to date, was 18 prompts away from reaching the high compliance bonus, and had earned US $21 in incentives.

### Study Implementation

The entirety of the study was conducted in REDCap, which is a free survey platform that allows researchers to create and manage surveys to collect data securely. The complex study was designed and implemented in a way that was fully automated.

Specifically, we created a project consisting of multiple surveys: a screener, a baseline survey, 4 momentary surveys (1 for each time of day: 11 AM, 2 PM, 5 PM, and 8 PM) for the EMA portion of the study, and an exit survey. Surveys were used to store participants’ contact information separately from the rest of the data. These surveys were uploaded by the research team for all potential participants. This triggered the automated survey invitations for these individuals to go out at a scheduled date and time. At each prompt, these automated invitations provided unique participant links to the screener survey.

The screener survey contained the consent form, as well as several eligibility-related questions. Once a participant clicked on the link and completed the screener, they were told whether they were eligible to continue. The survey ended for participants who were not eligible to continue, but they were provided with study team contact information if they had further questions.

Participants who were eligible after the screener survey were automatically forwarded to the baseline survey. After completing the baseline survey, each participant was redirected to a server maintained by the institution’s survey research center. This server randomly assigned each participant to the EMA or the EMA+DD condition and scheduled all 84 prompt invitations via texts using Twilio’s Multimedia Messaging service. For the EMA group, all 84 invitations would simply include the text “It’s time to complete your next survey:” with a link to the EMA survey in REDCap corresponding to that time of day.

For the EMA+DD group, on each of the 21 study days, the server would randomly select 1 of 4 prompts at which to deliver the DD. At the other 3 prompts during that day, participants would receive the standard message that was used for all prompts in the EMA group. Just before each prompt, if a participant was randomly determined to receive a DD at that prompt, the server used JavaScript libraries to calculate the compliance data for each participant and then generated a visual image showing their progress to date in the study, to be delivered at that prompt.

Participants were given 1 hour to complete each survey after receiving the invitation via text. The invitation links in the text messages took the participant to the server and forwarded them to the relevant REDCap survey only if the link was clicked within the designated timeframe and the participant had not already completed that prompt.

At 11 AM on the day following the 21st day of the EMA study, all participants in both groups received a link to an exit survey, which assessed their experiences while participating in the study. Participants had 7 days to complete the exit survey.

### Outcome Measures

#### Primary Outcomes

This study focused on 2 objective measures of compliance and a set of quantitative and qualitative measures of subjective experiences. Primary outcomes included the following:

Overall compliance: overall compliance was derived from a moment-level binary measure of compliance (ie, an indicator of whether the participant completed the survey within 60 minutes of a particular prompt), summed across 84 prompts within an individual. This was used to address the question: “Did individuals who received a daily DD complete a greater number of surveys, on average, compared to those who did not?”Average time of survey response: average time was derived from the length of time between the survey prompt and survey completion (among completed surveys), averaged across up to 84 prompts. This outcome was used to address the question: “Did participants who received the DD complete surveys more quickly, on average, compared to those who did not?”Subjective experiences of the study protocol: subjective experiences were assessed in the exit survey and were compared across groups. This comparison relied on both quantitative and qualitative measures of experiences.

#### Secondary Outcomes

Total number of surveys completed within each week, to compare whether participants were more likely to comply to the EMA protocol during week 1, 2, or 3, and whether the intervention effect varied across weeks.Mean time to complete surveys (among completed surveys) within each week.Total number of surveys completed within each day, to compare whether participants were more likely to comply to the EMA protocol across days 1 through 21, and whether they were more likely to comply on weekdays versus weekends. These differences also were examined to see whether the intervention effect varied across days or types of days.Mean time to complete surveys (among completed surveys) within each day.The moment-level binary indicator of compliance and moment-level length of time to complete each survey will be used as outcomes in multilevel models examining moment-level predictors of compliance (eg, time of day and whether they completed last survey) and moment-level predictors of time to complete surveys (eg, whether currently using phone, stress, positive affect, and negative affect). Group assignment will be included as a moderator to see whether the intervention effect varies across types of moments.(For the EMA+DD group only) Themoment-levelbinary indicator of compliance and moment-level length of time to complete each survey will be examined in relation to whether the DD was included at that prompt.

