However, compliance—particularly in substance use studies—can be a major concern for several reasons. First, young adults are less likely to complete reports on weekends when substance use is more likely to occur [5,6] and thus most critical to assess. Second, particular types of substance use behaviors, such as combining alcohol and cannabis, occurs somewhat rarely [7]. These behaviors can only be captured with many days of assessment, but participant compliance and motivation to participate in the study protocol may wane over time. Third, to assess behavior in optimal windows and provide timely intervention content, in some cases it is critical to assess behavior *in the moment when risk factors are higher*. However, engagement in the study protocol has the potential to interfere with participants’ daily lives. If young adults feel burdened by intensive longitudinal data collection, they may be less likely to provide complete data. A meta-analysis by Jones et al [8] concludes that overall, EMA compliance is only approximately 75% among individuals who use substances. Few studies have examined ways to improve participant compliance during intensive longitudinal data collection, yet recent work suggests that personalizing messages to young adults may increase compliance [9].

Mobile health apps have been developed in efforts to improve symptoms related to mental health, substance use, and a variety of other chronic health conditions and health behaviors. Many of these apps have shown no efficacy and/or modest clinical effects [10]. Poor engagement and related factors (eg, compliance, retention, and dropout) likely contribute to these findings because poor engagement with intervention content greatly weakens therapeutic effects. Only recently have studies of mobile health apps included measures of engagement as important outcomes; some even include aspects of engagement as the focus of interventions [11,12]. Among a wide variety of mobile health apps for managing chronic conditions (eg, mental well-being and HIV medication adherence), a meta-analysis estimated that the pooled dropout rate across apps was 43%, though the duration (range: 2 weeks to 1 year) and characteristics of study design varied considerably [13]. In another meta-analysis of apps addressing mental health problems, the dropout rate was approximately 36% after 8 weeks [11].

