## Results

Recruitment invitations were sent via direct email to 411 individuals. Of these, 92 (22%) completed the consent form, completed the baseline survey, and were randomized to either the EMA group or the EMA+DD group. Among these individuals, 91 (99%) ultimately participated in the EMA survey (ie, provided data at 1 or more EMA prompt), thus determining our final sample size. Data were collected during March and April 2023.

Participants were predominantly White (92%), non-Hispanic (89%), and female (67%), with a mean age of 20.3 (SD 1.18) years. Among the 91 participants, 43 (47%) were randomized to the EMA group and 48 (53%) were randomized to the EMA+DD group. Overall study compliance was very good, with a mean of 64.3 (14.6) out of 84 (76.5%) prompts completed, resulting in a total of 5896 (out of a possible 7644) person-moments of data.

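### Moderation of the group effect by completion of the last survey is not a randomised contrast, and can look real when it is not if the dashboard changes how much individuals differ in waning or if people disengage for good

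*Protocol article*

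**What the plan says.** Secondary Outcomes in the protocol article say that moment-level completion and response time "will be used as outcomes in multilevel models examining moment-level predictors of compliance" and of response time. The examples for completion are "moment-level predictors of compliance (eg, time of day and whether they completed last survey"). The next sentence reads "Group assignment will be included as a moderator to see whether the intervention effect varies across types of moments". A group by last-survey interaction is therefore planned, and it is to be read as effect modification.

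Participants and Trial Design places allocation before the first prompt: "Eligible participants who consented to participate in this study were randomized into either the EMA group or the EMA+DD group". Primary Outcomes ask whether dashboard recipients "complete a greater number of surveys, on average, compared to those who did not". On the course of compliance, the Overview says only that "participant compliance and motivation to participate in the study protocol may wane over time". For day-level outcomes the article does look at change over time: "These differences also were examined to see whether the intervention effect varied across days or types of days".

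**The concern.** Every value of last-survey completion is observed after allocation, and completion is what the dashboard is meant to raise. If the dashboard works, the people and days behind a missed last survey differ between arms. The arm difference within that stratum, and its contrast with the other stratum, are then no longer protected by randomisation.

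There is also a modelling problem. A random intercept absorbs stable differences between people but not person-specific drift. Leftover drift makes successive responses resemble each other, and the lag coefficient picks this up. If the leftover drift is larger in one arm, the lag coefficient is inflated more there, and the difference appears as an arm by lag interaction.

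At stake is a secondary claim that the dashboard works differently after a missed survey. A reader could take that as a tailoring rule although no such dependence exists.

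**Working it through.** **Inputs from the article.** Arms: "43 (47%) were randomized to the EMA group and 48 (53%) were randomized to the EMA+DD group". There are 84 prompts per person, and the mean (SD) completed is 64.3 (14.6). Check: 64.3/84 = 76.5% and 91 × 84 = 7644, both as stated. (The reported 5896 person-moments give 5896/7644 = 77.1%; the small gap does not matter here.)

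**Assumptions not in the article.** A 5% two-sided test, and a logit of completion equal to a person intercept (SD 1.1) plus a person slope over the study. Moderate drift: slope mean -1.0, SD 1.5. Steep drift: mean -1.6, SD 2.5. No scenario contains a true lag effect or a true group by lag interaction.

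**Why spread matters more than mean.** With only a random intercept, the covariance left between neighbouring responses grows with the between-person variance of the slope. Halving every slope in the dashboard arm also halves its SD:

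- moderate: 1.5² = 2.25 against 0.75² = 0.5625, a ratio of 4;
- steep: 2.5² = 6.25 against 1.25² = 1.5625, also 4.

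Group by day removes the difference in mean drift but not this difference in spread.

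**Simulation, dashboard halves each person's drift; random intercept, day and group by day in the model.** Ranges span repeated sets, mostly of 400 to 1,000 trials. The logistic 13% rests on 120 trials, with a Monte Carlo SE of √(0.13 × 0.87/120) ≈ 3 points.

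| Drift | Linear: interaction; rejection, model-based / cluster-robust SE | Logistic: log-odds; rejection, model-based / robust SE |
|---|---|---|
| Moderate | -2.8 to -3.2 points; 26-32% / 19-23% | -0.13; 13-16% / 14% |
| Steep | -5.6 to -6.1 points; 62-70% / 45-50% | -0.21; 33% / 26% |
| None (constant person effects) | 0 to -1.2 points; 6-10% / 6% | 0; 6% / 6% |

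A negative value means the dashboard appears to help more after a missed survey. Pooled SD is about 15 to 16 under moderate drift and about 17 to 17.5 under steep drift, so the steep case sits further from the reported 14.6.

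**What removes the bias.**

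- Same fall in mean drift but equal spread in both arms (linear model): -0.3 to -0.9 points. Rejection is 7-9% with robust SEs. Model-based rejection was 14% (moderate) and 20% (steep), which reflects an understated SE.
- A random day slope added to the linear model: moderate -0.9 points, 12%; steep -1.5 points, 13%.

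**Logistic random-intercept model, other forms of waning (1,000 trials each).** Rejection with no time term / day / day and group by day:

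- everyone wanes alike: 4.8-7.2% across all three models, with or without a dashboard odds ratio of 1.65;
- odds ratio 1.65 with strongly person-varying waning of equal spread in the arms: 19.4 / 10.5 / 9.1%;
- dashboard slows a fall common to all within an arm (logit -1.5 EMA, -0.5 EMA+DD): 23.1 / 9.2 / 5.6%;
- permanent disengagement, equal hazard, no dashboard effect: 40.5 / 38.0 / 35.8%. The mean interaction is about 0, but the estimates vary with SD 0.300 against a mean SE of 0.143 in the fullest model;
- permanent disengagement, hazard five times as high in the EMA arm: 82.2 / 80.6 / 78.0%, with a mean interaction of -0.505 log-odds in the fullest model.

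**The case against.** The strongest reply is that the numbers come from assumptions the article does not make. A reader might infer that the protocol expects the kind of waning that causes the error. It does not: the Overview says compliance may wane, and gives no rate, no variation between people and no difference by arm. If everyone wanes alike, the test holds its level. A dashboard that slows only average waning does not cause the bias either, once group by day is included. This stands, and it limits the claim to particular forms of waning.

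The model is also open. The article says multilevel, without fixing the link, the time terms or the random slopes. A condensed article may leave these to the analysis plan, so their absence is no defect, and a logistic model or random slopes give smaller errors. That stands too.

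A reader might further infer that the trial's just-in-time conclusions rest on this interaction. The Introduction ties that purpose to the microrandomised comparison within EMA+DD, and the last item of Secondary Outcomes already plans a within-arm analysis by dashboard receipt. The point concerns one example predictor in a secondary model, in what the Discussion calls a feasibility study.

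Under disengagement, part of the excess rejection is SE misspecification. If the dashboard does raise completion, part of the interaction may even be real, because it cannot act on people who have left.

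None of this makes last-survey completion a pre-randomisation variable. The planned reading of the interaction as variation in the intervention effect remains unsupported by the randomisation.

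**Conclusion.** The concern holds in a limited form. Group by last-survey completion conditions on a lagged primary outcome that the arm can change, so it does not identify moderation of a randomised effect. Spurious moderation is possible rather than certain. It needs arms that differ in how widely individuals drift, or permanent disengagement; person-varying drift of equal spread mainly understates the SE.

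Under the assumed halving of individual drift, rejection at a nominal 5% is roughly 20-30% in a linear model and 13-16% in a logistic one. Steep drift raises this to 45-70% and 26-33%. These sizes illustrate the mechanism and do not predict this trial's result. The stronger readings, that waning alone produces the error or that the trial's main result is compromised, are not supported: the primary comparison of total completed surveys by arm does not use this term.

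**What to change.** - For inference on whether the group effect varies, interact group only with features fixed by design or at baseline: time of day, study day, weekday or weekend, and baseline characteristics.
- If group by last-survey completion is reported, label it descriptive and fit it with group by day and person-specific day slopes. These slopes reduce the gradual-drift bias. They were not tested against permanent disengagement, where group by day alone left 36-78% rejection.
- Address recent compliance within the EMA+DD arm, by moderating the randomised dashboard/no-dashboard contrast by the previous day's completion. That is known before the day's slot takes effect, so each of the four slots keeps probability 1/4. The previous prompt on the same day is less suitable, because with one dashboard per day the chance at later prompts depends on what was already sent.

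The cost is a change of wording in the analysis plan, with no new data. The recent-compliance question then rests on 48 participants rather than 91, and it concerns the momentary effect of a dashboard rather than the effect of being in the dashboard arm.
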